## Abstract

**Background:**

Recent developments in eHealth and mobile health (mHealth), as well as the introduction of information and communication technology innovations in clinical practice, such as telemedicine, telemonitoring, and remote examinations, are already changing the current scenario and will continue to generate innovations in the coming decades. The widespread use of mobile devices, with an estimated nearly 30 billion devices and more than 325,000 apps worldwide, will provide various opportunities for people to take control of their own health. Already in 2017, most of the apps available were focused on pregnancy support, more than any other medical field. There have been some reported experiences with social media and mHealth that could benefit the promotion of maternal physical and mental health during pregnancy. However, many apps targeting the first 1000 days of a child’s life do not consider the continuity between the prenatal and postnatal periods and their joint impact on maternal and child health. The aim of this study is to evaluate the effectiveness of this mHealth app to support women during the first 1000 days (from conception to 24 months of age) and to improve health prevention behaviours such as immunizations during pregnancy, weight gain during pregnancy, abstinence from smoking and alcohol consumption, and adherence to the routine childhood immunization schedule. In addition, the study aims to understand the level of appreciation of this mHealth app as a tool to overcome information and communication gaps between patients and institutions.

**Methods:**

Conduction of a randomized controlled trial.

**Discussion:**

Our results will be relevant for improving this mHealth app to promote health and prevention and to support the first 1000 days of life for both mother and child. Our results will be relevant to the future expansion of such an mHealth app to promote positive health-related outcomes in patients and co-user satisfaction and to support the organization of health services.

**Trial registration:**

ClinicalTrials.gov NCT05500339.

**Supplementary Information:**

The online version contains supplementary material available at 10.1186/s13063-022-06953-y.

## Administrative information

Note: the numbers in curly brackets in this protocol refer to SPIRIT checklist item numbers. The order of the items has been modified to group similar items (see http://www.equator-network.org/reporting-guidelines/spirit-2013-statement-defining-standard-protocol-items-for-clinical-trials/).

## Introduction

### Background and rationale {6a}

Recent developments in eHealth and mobile health (mHealth), as well as the introduction of information and communication technology innovations in clinical practice, such as telemedicine, telemonitoring, and remote examinations, are already changing the current scenario and will bring about further innovations in the coming decades [1]. The widespread use of mobile devices, with an estimated nearly 30 billion devices [2] and more than 325,000 apps worldwide [3], will provide various opportunities for people to take control of their own health [4–6]. Already in 2017, most of the available apps focused on pregnancy support, more than any other medical field [7]. These mobile technologies for pregnancy support have also expanded the opportunities for parents and parents-to-be to self-manage health issues [8]. Results from a recent study conducted in Switzerland in 2019 showed that 91% of parents reported using digital media to search for information about their child’s health and development [8]. Some social media and mHealth experiences have been shown to be beneficial in promoting maternal physical and mental health during pregnancy [4]. However, many apps targeting the first 1000 days of life do not consider the continuity between the prenatal and postnatal periods and their joint impact on maternal and child health [9]. Moreover, the reliability, quality, and effectiveness of available pregnancy and postnatal care apps are still unclear. The potential negative consequences of misleading healthcare and lifestyle information or unnecessary worry and stress during pregnancy are of concern because women are more sensitive to external influences [10, 11]. Given the wide variability of apps in terms of ownership, responsibility, and updating of content, as well as the degree of reliability of the source [12], and the lack of a standardized certification system [12, 13], this limited evidence for their effectiveness is not surprising [10]. Furthermore, the standard design and development of apps do not usually take into account the level of health literacy of the target audience [13, 14], leaving the choice of which mHealth app to use to the preferences of users in terms of aesthetic, functional, and engagement aspects, regardless of the validity of the content provided or privacy and security considerations [15]. Considering that the first 1000 days of life represent a critical window of time for the child development, and given the critical influence of the health information source on maternal well-being, lifestyle, and decision-making related to pregnancy and child health [16], we have classified this as a burning issue that warrants further investigation.

### Objectives {7}

People are increasingly using eHealth and mobile health solutions thanks to the ease of access and rapid communication digital solutions provide. While this brings a variety of benefits and new opportunities, it may also pose a threat to public health in terms of prevention and health promotion by exposing them to potential risks such as lack of control and fake news.

The authors seek to answer the following research questions:Is an mHealth app a potential tool to bridge information and communication gaps between patients and institutions in the first 1000 days of life?What are the health and social implications of a patient- and family-centred mHealth application in a maternal and child health institute?Could such a tool be useful for supporting pregnant women and new mothers in the first 1000 days of life?Could such an mHealth tool be used at a regional or national level to improve the relationship between citizens and healthcare providers?

The primary aim is to evaluate the effectiveness of the mHealth app in supporting women in the first 1000 days (from conception to 24 months of life) and improving health behaviours, e.g. immunizations during pregnancy, weight gain during pregnancy, abstaining from smoking and alcohol consumption, and adherence to the routine childhood immunization schedule.

The secondary aim is to explore the level of appreciation of this mHealth app as a tool to bridge information and communication gaps between patients and healthcare providers.

Our findings will be relevant to improving this mHealth app to promote health and prevention and support the first 1000 days of life for mothers and children. Our findings will be relevant to the future expansion of such an mHealth app to promote positive health-related outcomes for patients and co-user satisfaction and to support the organization of healthcare services.

### Trial design {8}

Randomized, open-label, controlled trial to prospectively evaluate the superiority of care delivered with the support of the mHealth app over standard care.

## Methods: participants, interventions, and outcomes

### Study setting {9}

The study population is pregnant women attending the Unit of Fetal Medicine and Prenatal Diagnosis for first-trimester echography during pregnancy. Enrolment and subsequent data collection will be performed at Unit of Fetal Medicine and Prenatal Diagnosis, Institute for Maternal and Child Health - IRCCS "Burlo Garofolo", Trieste, Italy; analyses will be performed by Clinical Epidemiology and Healthcare Services Research, Institute for Maternal and Child Health - IRCCS "Burlo Garofolo", Trieste, Italy.

### Eligibility criteria {10}

Inclusion criteria are as follows: age ≥ 18 years, good understanding of the Italian language, possession of a smartphone for the app download, and willingness to deliver at the Institute for Maternal and Child Health - IRCCS "Burlo Garofolo", Trieste, Italy.

Exclusion criteria are as follows: individuals with cognitive impairments and individuals unable to give consent in person.

### Who will take informed consent? {26a}

Participants will be asked by the researcher to provide informed consent for study participation and data collection and management in accordance with the European General Data Protection Regulation (GDPR) and Italian law D.Lgs. 101/2018.

### Additional consent provisions for collection and use of participant data and biological specimens {26b}

In the consent form, participants are asked for permission for the research team to use and share data in aggregate form or from supervisory authorities, as relevant. No biological samples will be collected as part of this study.

### Explanation for the choice of comparators {6b}

Standard care was chosen as the comparator because pregnant women in clinical practice are usually educated by health professionals about preventive health and health promotion (e.g. to improve their preventive behaviours such as immunizations during pregnancy, weight gain during pregnancy, abstaining from smoking and alcohol consumption, and adherence to the routine childhood immunization schedule).

### Intervention description {11a}

Both groups of women (A and B) will be asked to complete an initial questionnaire to collect demographic and other data at time zero (T0). This paper questionnaire includes questions on health literacy, knowledge, and attitudes toward prevention and health promotion behaviours. At the same time, women in the experimental group will be assisted to download and instal the mHealth app on their smartphone or tablet.

During the study period, women in group A will be able to use the app, which was developed in collaboration with Area Science Park to support the first 1000 days of life, with all its features and content, while women in group B will be exposed to standard care. Specific content will be presented to the user according to the current pregnancy trimester or postpartum period following a scheduled routine; in any case, all content will always be available for free consultation throughout the usage period. Links to relevant institutional websites for further information will also be provided. The app will also include a FAQ (frequently asked question) section and a calendar function with the ability to set appointments and reminders. The app’s content and topics will include information on health preventive behaviours such as immunizations during pregnancy, weight gain during pregnancy, smoking abstinence and alcohol use, and adherence to routine childhood immunization schedules. The app will be an informative and educational tool aimed at improving health behaviours and well-being.

Three additional questionnaires will be collected from both groups of women during the study period at the end of the second and third trimesters (T1–2) and during the postpartum period (T3). While the second and third questionnaires will be distributed in printed form according to the women’s planned access to the Unit of Fetal Medicine and Prenatal Diagnosis, IRCCS "Burlo Garofolo", the fourth questionnaire will be made available online on the IRCCS "Burlo Garofolo" platform and in the app itself. Women will be reminded to complete it through the app’s calendar function and through email and phone reminders.

At the end of the trial period, women will also be asked to rate their appreciation of the app features and content by providing feedbacks in digital form and participating in focus group sessions.

Data on app use (frequency of app access, content consultation, references consultation, use of app features, etc.), access to and use of health services, and vaccination adherence during pregnancy will also be collected with support from the regional health information systems.

### Criteria for discontinuing or modifying allocated interventions {11b}

If any of the following clinical situations occur during the study period in women already enrolled, this will be grounds for exclusion of the patient from the study: intrauterine death, severe foetal malformation, miscarriage, and therapeutic abortion.

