### Sample size {14}

Given that 55% of pregnant women living in Trieste received the DPT vaccine during pregnancy in 2018, and assuming that this rate increases to 70%, a sample size of 163 women per group (total of 326 women) with an alpha of 0.05 and a beta of 0.2 is required. Considering the possibility of spontaneous abortion and the possibility of losing participants during the follow-up period, the investigators determined to recruit 180 women per group (360 women in total).

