## Assignment of interventions: allocation

### Sequence generation {16a}

Randomization will be open and will consider enrolment days. Eligible participants will be randomly assigned in a 1:1 ratio to the intervention group (use of the mHealth app) or to the control group (standard care). Enrolled women will be randomly assigned to two groups (the experimental group (A) and the control group (B)) using PC-driven randomization of enrolment days. This will facilitate enrolment as the researcher can give more information and train the groups of women to download and initialize the app.

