## Statistical methods

### Statistical methods for primary and secondary outcomes {20a}

Categorical variables will be presented as absolute numbers and percentages; continuous variables will be presented as mean and standard deviation or median and interquartile range, depending on data distribution assessed visually and using the Kolmogorov–Smirnov test.

The main population characteristics of the participating women in both groups (age, marital status, living area, country of origin, socioeconomic level, educational and occupational level, etc.) will be compared to assess the effectiveness of randomization. Differences between the two groups on categorical outcomes will be assessed using the chi-square test or Fisher’s exact test, as appropriate. Comparisons between continuous variables will be made with nonparametric Student *T* or Mann–Whitney tests, as appropriate for the data distribution. The main analysis will be an ‘intention-to-treat design’: all randomized women with an available main outcome will be assigned to the associated group regardless of intervention. A per-protocol analysis will also be performed. A statistically significant difference will be considered to exist if the *p*-value is < 0.05.

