### Methods in analysis to handle protocol non-adherence and any statistical methods to handle missing data {20c}

The main analysis will be performed as an ‘intention-to-treat’. All randomized women with an available main outcome will be analysed in the group to which they were randomized, regardless of whether they received the assigned intervention. Reasons for dropping out of the study will be detailed, and the potential impact of missing data on study outcomes will be explored through sensitivity analysis.

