### Adverse event reporting and harms {22}

Available data suggest that serious adverse events are not expected. Any adverse events, even if not related to the use of the app, but occurring during study conduct, will be reported to the relevant regulatory authorities in accordance with national legislation, specifying seriousness, severity, and causality.

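### Excluding enrolled women from the study after four pregnancy events conflicts with the intention-to-treat rule, and the plan does not say whether the regional vaccination record can supply a missing main outcome

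*Protocol article*

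**What the plan says.** **Exclusion.** Criteria for discontinuing or modifying allocated interventions {11b} begins "If any of the following clinical situations occur during the study period in women already enrolled" and continues that "this will be grounds for exclusion of the patient from the study". The events it lists are miscarriage, therapeutic abortion, intrauterine death and severe foetal malformation. The heading concerns the intervention, but the sentence removes the woman from the study.

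**Analysis set.** Statistical methods {20a} states that "all randomized women with an available main outcome will be assigned to the associated group regardless of intervention". Section {20c} repeats this under the intention-to-treat label, promises to detail reasons for dropout, and plans a sensitivity analysis for missing data. A per-protocol analysis is planned separately.

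**Allocation.** Sequence generation {16a} assigns women "using PC-driven randomization of enrolment days". The trial is open-label {17a}.

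**Outcome source.** Outcomes {12} ties the primary outcome, DPT vaccination in pregnancy, to the questionnaires, evaluated postpartum (T3). Intervention description {11a} says that vaccination adherence will also be collected with support from regional systems. Data management {19} merges the health information system into the final data set. Participant timeline {13} and section {18a} say only that such data can be accessed to confirm adherence.

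**Losses.** Sample size {14} goes from 163 to 180 per group: "Considering the possibility of spontaneous abortion and the possibility of losing participants during the follow-up period".

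**The concern.** An intention-to-treat comparison keeps every woman in the arm to which she was allocated, whatever happens later. Section {11b} takes women out because of events after allocation, and some of them will have a known DPT status. Two examples are a continuing pregnancy with a severe malformation and a late intrauterine death after vaccination was offered. Two analysts following the article could build different primary sets, and both could cite its text.

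The open-label design adds to this. Three of the four events leave little room for discretion, but the article does not define a severe malformation, and the people making that judgement can know the arm.

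The second gap concerns whose outcome counts as available. According to {11a}, the T3 questionnaire is offered on the institute's platform and inside the app, with reminders through the app calendar as well as by email and phone. Only group A has the app. If the questionnaire is the sole source, availability of the primary outcome can depend on arm. If the regional record also counts, most of that dependence goes. The article does not say which applies.

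**Working it through.** **1. The rules side by side**, for an enrolled woman with one of the four events:

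| Her DPT status | {11b} | {20a} and {20c} |
|---|---|---|
| Known | Out of the study | Analysed in her allocated arm |
| Not known | Out of the study | Not in the main set; missing-data sensitivity analysis |
| Pregnancy ended before DPT could be offered | Out of the study | Not addressed |

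The first row is a direct conflict. {11b} applies to women already enrolled, and {16a} fixes the arm by enrolment day, so every exclusion comes after allocation.

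**2. The plan's own sample size.** Inputs from {14}: 55% and 70%, alpha 0.05 (taken as two-sided), power 80%. With pooled variance and no continuity correction, and mean rate 0.625:

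n = [1.960 × √(2 × 0.625 × 0.375) + 0.842 × √(0.55 × 0.45 + 0.70 × 0.30)]² / 0.15² = (1.342 + 0.569)² / 0.0225 ≈ 162.3, rounded up to **163**.

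This agrees with the plan. The allowance is 180 − 163 = 17 per arm, and 17/180 = 9.4%. It covers spontaneous abortion and loss to follow-up together.

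**3. How far the missing women could move an arm's rate.** Suppose that 163 women are observed at the planning rates and 17 are missing.

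- Control, all 17 unvaccinated: 0.55 × 163/180 = 49.8%, a move of −5.2 points.
- Control, all 17 vaccinated: (0.55 × 163 + 17)/180 = 59.3%, a move of +4.3 points.
- App, all 17 unvaccinated: 0.70 × 163/180 = 63.4%, a move of −6.6 points.
- App, all 17 vaccinated: (0.70 × 163 + 17)/180 = 72.8%, a move of +2.8 points.

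Each range is 9.4 points wide, but the largest move from the observed rate is 5.2 points in control and 6.6 points in the app arm. With opposite extremes in both arms at once, the 15-point difference would lie between 63.4 − 59.3 = 4.1 and 72.8 − 49.8 = 23.0. These are bounds, not expectations.

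**4. If the questionnaire were the only source.** The response rates here are assumed, with no true effect and 55% vaccinated. If 95% of vaccinated and 85% of unvaccinated women in one arm respond, that arm shows 0.5225/(0.5225 + 0.3825) = 57.7%. With 90% and 70% it shows 0.495/(0.495 + 0.315) = 61.1%. If missingness in the other arm is unrelated to vaccination, the spurious difference is 2.7 or 6.1 points.

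**5. Power if these women are kept.** At 55% against 70%, power is 80.2% with 163 per arm and 83.9% with all 180 known. No event share is stated. If 2%, 3% or 5% of each arm had an event and were counted as unvaccinated, power with 180 per arm would be 81.9%, 80.9% or 78.8%. These figures use the plan's own formula, which treats women as individually randomised.

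**The case against.** The strongest defence is that the article defines its set in the same sentence as the label, so nobody is misled about who is analysed. Miscarriage, intrauterine death and therapeutic abortion are clinical events, and the protocol anticipates no harm from the app. Exclusion that does not depend on arm need not bias the comparison. Setting aside a pregnancy that ended before DPT could be offered is reasonable. Much of this stands: the documents show no mechanism by which the app would change these event rates. It does not resolve the conflict for women with known status, nor the room for judgement over severe malformation.

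A reader might infer four stronger points. The documents do not support them.

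- *Women who do not return the T3 questionnaire are dropped.* Regional vaccination data are collected {11a} and merged {19}, so a non-responder may still have an available outcome. The fault is that the role of that record is not stated.
- *The events cannot be counted by arm.* They are themselves the reasons for exclusion, allocation is known, and {20c} promises reasons for dropout.
- *Adverse event reporting {22} is contradicted.* That section requires reports to authorities of "Any adverse events, even if not related to the use of the app". Leaving the analysis set does not stop such reports. Pregnancy loss and malformation are not listed outcomes, so no planned comparison is lost.
- *The risk difference could shift by 9.4 points through one arm.* That figure is the distance between two opposite extremes. The largest one-arm move is 6.6 points.

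The sensitivity analysis in {20c} is a real safeguard. It is not said to cover women removed under {11b}, who are excluded rather than missing.

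**Conclusion.** The point holds as a conflict of rules and an inexact label. {11b} and {20a}/{20c} give different answers for a woman with one of the four events and a known DPT status. The set that results is an available-case set with post-randomisation exclusions. The role of the regional record when the questionnaire is missing is also unsettled.

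The effect of {11b} alone cannot be sized, because the documents give no event rate. For all losses combined, assuming the budgeted 17 of 180 per arm and the planning rates, the move is at most about 5.2 points in control and 6.6 in the app arm, against a 15-point target. Those limits require every missing woman in an arm to have the same status, so the likely effect is smaller. No number in the plan is wrong. This should be corrected before the data are analysed, but it does not undermine the design.

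**What to change.** 1. Reconcile {11b} with {20a} and {20c}: after any of the four events, questionnaires and reminders stop, but the woman remains a randomised participant. This concerns data handling only, not her care.
2. Analyse all randomised women as allocated. State that the regional vaccination record supplies the main outcome where the T3 questionnaire is missing.
3. Set aside only pregnancies that ended before DPT could be offered, by one written rule applied blind to arm. Extend the sensitivity analysis already planned in {20c} to count these women as unvaccinated.
4. Tabulate the four events by arm.
5. Label any analysis limited to available outcomes as an available-case analysis.

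The cost is wording changes and a little more analysis. The data source is already planned, and these women need not be contacted again. Under the assumed event shares above, counting them as unvaccinated leaves power with 180 per arm between 78.8% and 81.9%.
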